The effectiveness of stroke interventions is often described by measures of disability, or functional assessment. Evaluations that deal with activities of daily living (ADLs) generally include the Functional Independence Measure, the Katz index and the Barthel index (BI), the latter being a prevalent measure for the clinical evaluation of stroke patients, with substantial supporting research [26–28]. However, there are few studies involving the ADLs as the primary outcome for a marker of functional recovery after neurostimulation. For example, in a systematic review where the efficacy of tDCS in ADLs and motor function after stroke were analyzed, the authors found that the results are inaccurate and the effect was not sustained when studies of high methodological quality were included. There were 15 studies involving a total of 455 participants included, with only randomized controlled trials and randomized controlled cross-over trials evaluated. Of the total, the analysis of five studies involving 286 participants to examine the effects of tDCS on our primary outcome (ADLs evaluated by BI) has shown that no effect was observed on the performance at the end of the intervention. In three studies from this systematic review involving 99 participants to evaluate the effects of tDCS in BI scores at the end of follow-up, evidence suggested an effect on the ADL performance, but the confidence intervals were wide, and the effect was not sustained when they only included studies with low risk of bias. Thus, the authors point to the need for future research in this area to improve the generalization of the results [29].

Although clinical trials can be found that measure the efficacy of tDCS in ADLs pointing to positive effects [30, 31] among other factors, in general they only include participants in the chronic stage with brain injuries in different areas and varying levels of functional incapacity.

Therefore, central questions remain: For a daily protocol of 10 days, does the active tDCS applied under a 2 mA current and associated with CIMT have a superior response to the simulated (placebo) current applied with CIMT, and if so, what is the size of the effect? What adverse effects are associated with the therapy? Does functional improvement in the ADLs persist over time?

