## Methods

### Overview

This is a placebo-controlled, double-blind, randomized clinical trial (Fig. 1), in which 40 patients are divided into two groups of 20 participants each. In Fig. 1, the CONSORT (Consolidated Standards of Reporting Trial) flowchart [32] shows the number and distribution of participants: Group A1 - participants in post-stroke subacute stage that receive active tDCS combined with CIMT; Group A2 - participants in the post-stroke subacute stage who receive a placebo stimulation associated with CIMT. Patients will undergo three assessments: baseline (T0), week 2 (T1), and week 4 (T2). Neuropsychological tests will be performed at T0 and T2. Adverse events will be measured in each session, where the researcher responsible for administering the neurostimulation will question the patient on whether they experience any uncomfortable or painful sensation, and if this is related to the tDCS, following the procedure of Brunoni et al. [33]. At the end of the study, participants who received tDCS and showed clinical improvement will be invited to receive bimonthly stimulation for 12 months as part of a longitudinal study of tDCS for stroke. Those who received the tDCS placebo and did not respond will be invited to receive daily sessions with an active current for 10 days. Finally, those who had a response to the placebo will be referred for other physical therapy treatment.

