While evaluating the efficiency of the masking mechanism [17], which is routine in studies for the treatment of stroke and other diseases related to neuromodulation, biases may occur due to inadequate blinding of several people involved in the clinical trial, or by error allocation, the effect of the treatment, or co-interventions [76]. Unlike blindness, these bias-generating consequences can be measured [77]. To this end, the example of another study using external judges [78] will be applied in this work, a final evaluation involving neurologist doctors accompanying the patients in their clinical treatment. These professionals will not be aware of behavior and interventions applied in this experiment. The imaging tests carried out for the diagnosis of vascular injury will be repeated and evaluated by these doctors at the end of intervention (T1) as a routine consultation procedure. After analysis of these imaging tests, the doctors will be asked whether they believe that the patient has suffered some consequential event which can act as an external assessment tool for a clinical trial. Reports of biased results can be examined as to whether the degree of agreement between the opinion of an external judge (neurologist) and the trialists (involved in outcome assessments and physical therapy interventions with CIMT) will be the same for both experimental and control participants.

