## Intervention

### Constraint-induced movement therapy (CIMT)

The CIMT will be held immediately after the patient has received a neurostimulation session. Daily 3-hour protocol motor skills training supervised by a therapist will be applied for two weeks (10 calendar days, excluding weekends), with non-affected limb restriction for 90 % of the patient’s waking time, as advocated in previous studies with patients after stroke [79]. The motor training conducted by a physiotherapist will cover the use of the paretic limb during ADLs, with the non-paretic arm restricted by a sling. The patient will be encouraged to use the affected limb during the daily routine of his/her activities.

Patients will be encouraged to keep a journal to document their workouts, recording the training time duration, activities done with the restriction sleeve, and main difficulties. The physiotherapist responsible for the treatment will review the diary weekly, which will allow for controlling and verifying compliance in the implementation of CIMT performed by the patient. If there is a discrepancy with the principles of the technique, adjustments and guidelines will be offered for the proper conduct of the protocol. It is important to clarify that the purpose of the restriction sleeve is not to encourage a permanent change in the way the patient performs daily activities, but to encourage the concentrated and repetitive use of the paretic upper limb, seeking a “use-dependent” cortical reorganization [80].

Thus, all participants, regardless of receiving active or simulated current, will be treated with CIMT during the 10 days of neurostimulation, respecting the ethical principles to ensure therapeutic assistance to those involved.

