### Data analyses

The design of the statistical analysis is based on previous studies of literature relating to clinical and placebo-controlled trials using tDCS [17, 30, 90, 91]. The intention-to-treat analysis will be used; however, high or differential rates of missing data between treatment arms/sides may indicate a departure from this assumption and may lead to bias [92]. Thus, a sensitivity analysis will be performed with different allocation procedures to verify the strength of the data. The best strategy resulting from the comparison of the following methods will be chosen: last observation carried forward, complete case analysis, likelihood-based methods, and multiple imputation [93]. As pointed out by White et al. [94] in the intention-to-treat analysis strategy, the main focus in the analysis of choice should be the plausibility of its assumptions, while the inclusion of all randomized individuals is a requirement only for sensitivity analysis.

Multivariate imputation by chained equations (MICE, the R Foundation for Statistical Computing, Vienna, Austria) and SPSS Ver.20.0 (SPSS Inc., Chicago, IL, USA) software will be used.

Regarding sociodemographic and clinical characteristics at the baseline, for continuous variables, information on the variability will be presented for example, mean and standard deviation). If groups are similar to each other, descriptive data analysis will be performed. However, if important differences are found, regression analysis will be used to evaluate these data to estimate the effects of covariates with the variables of interest.

Regarding clinical outcomes, the primary outcome will be analyzed with analysis of mean change scores (MCS) to the total score of BI. The MCS will be evaluated in three ways: change occurred between the post and pre-test (T1-T0); between endpoint and pre-test (T2-T0); between the endpoint and post-test (T2-T1). The baseline as covariate will be used to identify potential differences between the groups by analysis of covariance (ANCOVA) [95].

Finally, the effect sizes and confidence intervals of change scores will be calculated using Cohen’s *d*, using the Hedges correction, with values of 0.20, 0.50, and 0.80, reflecting small, medium, and large effects, respectively [96]. For all variables of the secondary outcomes, the same analysis strategy will be used. Non-parametric tests will be performed if some of the outcomes do not meet the conditions necessary for parametric analysis.

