## Discussion

The present work is a placebo-controlled, double-blind, randomized clinical trial developed to analyze the effectiveness of tDCS in activities of daily living of stroke patients. Regarding the sample, the majority of clinical trials involving neuromodulation and rehabilitation involve samples of 20 to 30 subjects and follow-up conducted for approximately three months [17, 100]. The use of a larger sample, with monitoring of the respondents to therapy during a year as proposed in this study reduces the risk of type II error, allowing for the possibility of expanding the generalization spectrum into other contexts related to tDCS.

Furthermore, although other studies have currently been developed on this subject, most of the work has methodological differences, such as lack of control on the type of stroke, lesion location, and characteristics of the participants [91]. Patients with ischemic stroke should not be directly compared with those who have had a hemorrhagic stroke; also, patients with multiple foci and extensive areas of injury should not be equated to those with mild or moderate degrees of compromise. Errors of this nature committed during the inclusion of the participants are methodological limitations, inhibiting confirmation or refutation of raised hypotheses.

In this sense, questions remain about at what moment after stroke tDCS therapy would be appropriate. Elsner et al. [29] developed a systematic review of the application of tDCS on motor function and ADLs, and verified the existence of three studies involving subacute patients, confirming that most of the work involves patients analyzed more than six months after the stroke. Therefore, there is need for controlled clinical trials evaluating the effect of this technique on patients in the early stages of a stroke.

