As for the therapies associated with neurostimulation, some studies include patients with tDCS not assisted by any intervention or uniformed treatment protocols [91, 99]. A Cochrane meta-analysis examined studies using physical therapy techniques used in post-stroke rehabilitation. Although the authors agree that physical therapy is a key part of rehabilitation, the study’s findings were not able to measure which technique was more effective than others. In this sense, the authors recommend that future research should focus on investigating the effectiveness of clearly described techniques and standard treatments for the tasks developed [29]. Another systematic review, which analyzed randomized controlled trials on the treatment of various therapies involving upper limbs after stroke, notes that there is a limitation in terms of scientific evidence of the benefits of conventional therapies such as stretching, passive exercises, and mobilization [101]. According to the authors, the methodological flaws involving these procedures do not make it clear how much therapy is to be provided, who should provide it, and how patients should be directed so that the functional gains are maximized.

The lack of control of these techniques with rehabilitation studies can bring forward biases with confounding variables in interpreting the results, beyond what prevents the replication of future studies in the area. Techniques not standardized can be considered inferior to the systematic protocols of physical therapy. Instead, the standard motor training, if coupled with tDCS, can guide the plasticity process towards a functional result, since tDCS activates a mass of circuits which receive neuromuscular feedback in a specific way [17]. Given these facts, standardized and systematic CIMT physical therapy was chosen for this study, taking into account that since the CIMT therapy may promote recovery through inter-hemispheric inhibition, the tDCS can also induce beneficial effects of focal mode, activating neural circuits in the damaged hemisphere [18].

Overall, this study will assess the effectiveness of tDCS combined with CIMT physical therapy protocol in subacute stage after-stroke patients, and analyze the maintenance of the benefits achieved over time through markers of functional recovery. Therefore, the results of this study may lead to implications for future clinical trials in this area.

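### Persistence of the ADL gain can be judged only about two weeks after treatment; the year of responder monitoring credited in the Discussion adds no power and cannot show durability

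*Protocol article*

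**What the plan says.** **The question.** The Background of the protocol article lists among its central questions "Does functional improvement in the ADLs persist over time". The Discussion says the study will "analyze the maintenance of the benefits achieved over time through markers of functional recovery". Neither place gives a time horizon.

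**The randomised schedule.** Under Overview, "Patients will undergo three assessments: baseline (T0), week 2 (T1), and week 4 (T2"). The therapy, delivered right after each stimulation session, "will be applied for two weeks (10 calendar days, excluding weekends"). The section on randomization and blinding places T1 "at the end of intervention (T1"). Data analyses names three change scores for the Barthel index (BI): T1-T0, T2-T0 and the change "between the endpoint and post-test (T2-T1").

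**After week 4 (Overview).**
- In the active arm, "participants who received tDCS and showed clinical improvement will be invited to receive bimonthly stimulation for 12 months as part of a longitudinal study".
- Placebo patients who did not respond are offered ten days of active current.
- Placebo patients who did respond are referred to other physical therapy.

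Outcomes defines clinical improvement by the BI at T2 against T0, with a threshold of 10 points.

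**The credit taken.** The Discussion first says that most comparable trials enrol 20 to 30 subjects and follow them for about three months. It then presents the larger sample together with "monitoring of the respondents to therapy during a year as proposed in this study" as lowering type II error and opening the way to wider generalisation.

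**The concern.** The Discussion gives the trial a property that its design lacks. A reader would take it that this trial watches patients for a year where others watch for about three months, and that this makes its conclusions stronger. The arms are in fact compared for four weeks from baseline. The year belongs to a subgroup of one arm, chosen on its own outcome and still being offered the treatment.

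What is at stake is what the trial may conclude on a question that it calls central. If responders still look improved after a year, three other explanations fit equally well: continued stimulation, natural recovery after a subacute stroke, and selection on an observed gain. None of them can be separated from a lasting effect of the 10-day course.

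**Working it through.** **1. Length of controlled observation after treatment.**
- End of treatment: week 2, from ten weekday sessions (CIMT section) and T1 as end of intervention (Randomization and blinding).
- Last assessment of both arms: week 4 (Overview).
- Interval: 4 − 2 = 2 weeks. It is somewhat shorter for a patient who makes up missed sessions in the following week, as Attrition and adherence allows.

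Within that window, T2-T0 shows whether the arms differ about two weeks off treatment. T2-T1 shows whether the gap has changed since treatment ended. Data analyses names no later contrast.

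**2. Does a year of responder monitoring lower type II error?** The plan's own figure comes first. Inputs from Sample size: difference 10 BI points, SD 7, power 90%, level 0.05 (two-sided assumed), 1:1 allocation.
- Normal approximation: n per group = 2 × (1.960 + 1.282)² × (7/10)² = 2 × 10.51 × 0.49 = 10.3, so 11.
- Two-sample t-test: 11.35, so 12. The stated 12 per group is reproduced.
- Power by t-test is 91.7% at 12 per group and 99.3% at 20 per group. Type II error is therefore 8.3% and 0.7%.

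On these inputs the larger sample does lower type II error. Length of monitoring after T2 is not an input to the calculation. Data collected after T2, in one arm only, cannot alter the test at T1 or T2.

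**3. Who is in the year-long group?**

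| Group at week 4 | What Overview describes | Usable as a concurrent control? |
|---|---|---|
| Active, improved | Invited to 12 months of further stimulation | This is the followed group |
| Active, not improved | Not mentioned | No |
| Placebo, not improved | Offered active current | No, the offer ends their use as controls |
| Placebo, improved | Referred to other physical therapy | No later assessment described |

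The document gives no response rate. Assuming 30% to 90% of the 20 active patients improve, the group is 20 × 0.30 = 6 to 20 × 0.90 = 18 patients, or 15% to 45% of the 40 randomised. The concurrent placebo comparison has 0 patients.

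**4. The contrast with other trials.** The Discussion cites about three months of follow-up elsewhere. The like-for-like figure here is the randomised follow-up of four weeks from baseline, which is shorter.

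**The case against.** The strongest reply is that the analysis is already sound. Data analyses uses only T0, T1 and T2, under intention to treat with baseline as covariate. Overview places the 12-month phase after the end of the study and within a longitudinal study, so it can be read as a separate project. A condensed article need not describe that project, nor what happens to active patients who do not improve. All of this stands, and it confines the point to claims and wording.

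Stronger readings are tempting, but the documents do not support them:
- **That a year of persistence was promised and is not delivered.** Background and Discussion say only that persistence or maintenance over time is of interest. The 12 months is the length of the stimulation offered afterwards, not a stated period of controlled observation. The week-4 comparison does give a short-term answer.
- **That the plan will produce a biased 12-month durability estimate.** No 12-month outcome, visit or test is specified. Putting a size on the selection effect would need the reliability of the BI change score, which is not given. It would also mean reading the 10 points under Sample size as the active arm's own gain, although they are used to size the difference between arms.
- **That all contact after week 4 is confined to active responders.** Placebo patients who did not respond are also offered treatment. The year of monitoring, however, is described only for responders.
- **That the year-long group is chosen for a high T2 score.** The criterion is improvement on baseline.

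What the reply does not remove is the Discussion sentence. It describes the year as proposed in this study and uses it to support this trial's power and reach. If the extension is a separate project, that argument falls for that reason as well.

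**Conclusion.** The point holds as a mismatch between claim and design. The randomised evidence on persistence covers about two weeks after the last session. The year of responder monitoring adds nothing to the power of the active-versus-sham comparison, and it cannot show that the effect of the 10-day course lasts or that it generalises further.

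This rests on the stated schedule and post-week-4 arrangements, and on reading improvement as a T0-to-T2 gain above 10 points. It does not depend on the assumed response rates, which only indicate how small the followed group may be. The planned T0, T1 and T2 analyses are not faulted here. The correction is still worth making, because it settles what the final report may say on a central question.

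**What to change.** Make these changes, in an erratum or update to the article or in the analysis plan and final report:

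1. **Background and Discussion (persistence and maintenance statements):** say that persistence is judged only from the randomised active-versus-sham BI comparison at week 4 (T2-T0 and T2-T1), about two weeks after the last session, in all randomised patients.
2. **Discussion (comparison with other trials):** remove the year-long monitoring and the type II error and generalisation claims attached to it. A statement about the larger sample can stand by itself. Give this trial's randomised follow-up as four weeks wherever it is set against about three months elsewhere.
3. **Overview:** label the 12-month stimulation phase and the offer of active current to placebo patients as uncontrolled extensions, from which no durability or efficacy conclusion is drawn.

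The cost is wording only. No visit, treatment arrangement or planned T0-T2 analysis changes. The downside is a more modest claim on duration.

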**Fig. 1 Fig1:**
[figure not shown]
CONSORT (Consolidated Standards of Reporting Trials) flowchart of the clinical trial. BI: Barthel index; CIMT: constraint-induced movement therapy; MMSE, Mini Mental State Examination; MoCA: Montreal Cognitive Assessment; MRC: Medical Research Council (scale); NIHSS, National Institutes of Health Stroke Scale; PASS: Postural Assessment Scale for Stroke; SF-36: Medical Outcomes Study 36-item Short-Form Health Survey; SPPB: Short Physical Performance Battery; tDCS, transcranial direct current stimulation; WMFT: Wolf Motor Function Test

### Patients and enrollment

Participants will undergo neurological, neuropsychological, and physical therapy evaluation performed by specialists in each area as the eligibility criteria for selection.

### Inclusion criteria

Patients will be selected according to the following inclusion criteria: a) age between 18 and 65 years; b) diagnosis of unilateral, non-recurring, subacute stroke of ischemic and lacunar type, as defined by the International Classification of Diseases (ICD-10) through computed tomography or magnetic resonance imaging conducted by neurologists; c) a score < 1 on the consciousness and communication items of the National Institutes of Health Stroke Scale (NIHSS) [34]; and d) the patient provided written informed consent.

Although the subacute phase of stroke generally comprises the period of 7 to 90 days after injury [35–38], this study will only include those at 1–3 months after stroke to avoid the inclusion of participants in the acute phase. The definition of the age group followed the age interval often found in studies involving tDCS and stroke [17, 39, 40]. However, for a more conservative position of experimental control, we preferred to limit the inclusion up to 65 years of age to avoid this variable possibly interfering in the performance of elderly participants, as this could increase the chances that there are other conditions associated with aging (such as concentration and memory).

